### Sample size

A sample size of 86 clinics (clusters), with a minimum of one GP per cluster and assuming a GP dropout rate of 25%, has >80% power to detect a medium-large effect size of Cohen’s d of 0.69 (assuming a GP-level outcome score change of 1.2 on a scale with score range of 0 to 9 and a standard deviation of 1.75 as identified in a pilot study of the primary outcome tool; correlation between baseline and follow-up measurements of 0.3, and two-sided significance of 0.05).

We estimate that each GP cluster will recruit a minimum of 7 and a maximum of 24 patients (the cut-off to ensure that the patient sample is not skewed by a high-recruiting cluster) over the study period. Based on our analysis of high-caseload GPs [32], we estimate that there will be approximately 22 eligible patients/year/GP. Accounting for a 66% estimated rate of refusal to participate as observed in another study that recruited participants with mental health conditions in the Australian general practice setting [33], we estimate that at least 7 eligible patients will be successfully recruited by each participating GP in a 9-month period.

We anticipate that approximately 448 patients who are recruited within the 9 months (224 from control clinics and 224 test clinics; 7 per clinic/cluster) will have 3-month data. These patient numbers assume up to 25% of the 86 recruited GPs will drop out of the study. Using data from these patients, we will have 90% power to detect medium effects (Cohen’s d = 0.5) in secondary outcome measures between two groups (test/control) at 3 months. Calculations assume an alpha of 0.01, ICC of 0.03, and correlation of 0.5 between individual scores. Calculations were made using Cluster statistical software [34].

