### Statistical methods

#### Primary analysis

The main analysis examining the primary outcome (proportion of guideline concordance) will be intention to treat using multilevel regression models (linear or Poisson regression, as appropriate), with time-point and intervention status as fixed effects. Clusters will be examined as a random effect for inclusion into the model. Covariates will include the stratification factors, which are state, clinic size (GP equivalent full time >5 (yes/no)), and location (urban vs regional/rural).

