#### Secondary analysis

*Patient analyses*: Using a similar mixed model approach as in the main analyses, changes in patient health status (using the SF-36 v2), and work participation (using relevant measures of the National Return To Work Survey) will be measured by comparing the scores on patient surveys from baseline to 3, 6, and 9 months following their initial GP consultation.

*Adjusted analyses*: The main analysis and subgroup analyses above include adjustment for the stratification factors, which are state, clinic size (GP equivalent full time >5 (yes/no)), and location (urban vs regional/rural), additional mental health training.

*Missing data*: As the GP and patient-level data are longitudinal samples, a missing data analysis will be done on each longitudinal data set and investigations made for predictors of missingness. These investigations will examine the effect of key demographic and other factors particularly on the presence of missing outcomes. If outcome data is found to not be missing at random, then multiple imputation will be applied using the predictors for missingness.

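### The missing-data rule chooses imputation variables because they predict missingness and does not require trial arm, so an imputed analysis could dilute the arm effect by about the missing fraction

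*Protocol article*

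**What the plan says.** In the protocol article, Statistical methods, the Missing data paragraph under Secondary analysis covers both the GP and the patient data sets. It sets out three steps.

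- A search for predictors of missingness: "These investigations will examine the effect of key demographic and other factors particularly on the presence of missing outcomes".
- A condition: "If outcome data is found to not be missing at random".
- The action if that condition is met: "then multiple imputation will be applied using the predictors for missingness".

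The Primary analysis paragraph describes a multilevel regression "with time-point and intervention status as fixed effects", with the stratification factors as covariates. On clinic it says: "Clusters will be examined as a random effect for inclusion into the model".

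The missing-data paragraph does not refer back to that model. It does not say that arm, time-point, the stratification factors, clinic or a participant's other scores belong in the imputation. The Sample size section gives the scale of loss to expect among GPs: power is calculated "assuming a GP dropout rate of 25" per cent.

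**The concern.** Whether a variable predicts missingness is a reasonable test for adding auxiliary variables to an imputation model. It is the wrong test for the model's core. An imputation model should contain every term of the analysis it feeds, and arm above all, because the arm contrast is what is being estimated.

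Under the stated criterion, arm qualifies when dropout differs between arms. When dropout is similar, which is what one hopes for, arm does not qualify. The imputed scores then carry no arm difference and pull the two arms together. In that situation an analysis of the available data would estimate the arm effect with little or no bias, so imputing by the rule would make the result worse. The primary outcome is exposed, as are the patient outcomes, because the paragraph applies to both data sets.

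**Working it through.** **Inputs (Sample size section).** "A sample size of 86 clinics (clusters), with a minimum of one GP per cluster"; 25% GP dropout, taken here as the share of missing 9-month scores; "assuming a GP-level outcome score change of 1.2 on a scale with score range of 0 to 9 and a standard deviation of 1.75"; baseline to follow-up correlation 0.3; two-sided 0.05. Equal allocation and one GP per clinic are assumed.

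**The plan's own figure.**
- GPs remaining: 86 × 0.75 = 64.5, about 32 per arm.
- Baseline-adjusted SD: 1.75 × √(1 − 0.3²) = 1.669.
- Standard error: 1.669 × √(2/32) = 0.417.
- Power: Φ(1.2/0.417 − 1.96) = 0.82, or 0.81 with the t distribution.

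The stated power above 80% is reproduced.

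**Expected estimate with arm left out.** Let f be the missing fraction in each arm, μ₁ and μ₀ the arm means, and m the common mean of the imputed scores. After imputation the arm means are (1 − f)μ₁ + f·m and (1 − f)μ₀ + f·m. Their difference is (1 − f)(μ₁ − μ₀). For a true effect of 1.2:

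| Missing fraction | Expected estimate |
|---|---|
| 10% | 1.08 |
| 15% | 1.02 |
| 25% | 0.90 |
| 35% | 0.78 |

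If dropout were 35% in the intervention arm and 15% in control, and arm were still left out, the observed scores would be 0.65/(0.65 + 0.85) = 43.3% intervention. Setting μ₀ = 0 gives m = 0.433 × 1.2 = 0.52. The difference is 0.65 × 1.2 + (0.35 − 0.15) × 0.52 = 0.884. Under the stated rule arm might well enter in that case.

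**Simulation, GP outcome.** 86 GPs, 25% missing, missingness unrelated to arm, normal-regression imputation with 20 imputations and Rubin's rules, baseline-adjusted linear analysis, 2,500 to 3,000 trials per setting. Missingness was either purely random or dependent on a covariate included in the imputation.

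| Analysis | Mean estimate (true 1.2) | Power |
|---|---|---|
| Available cases | 1.20–1.21 | 80–82% |
| Imputation with arm and baseline | 1.20–1.21 | 78–80% |
| Imputation with arm, without baseline | 1.21 | 76–78% |
| Imputation with baseline, without arm | 0.89–0.90 | 54–57% |
| Imputation without arm or baseline | 0.90 | 53–54% |

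A further simulation on the same inputs gave about 0.91 and 56–59% power with arm out, and about 1.2 and 78% with arm in, with or without baseline. Together, power with arm out is about 53–59%. With dropout of 35% and 15% and arm forced out, the simulated mean was 0.885–0.890, close to the 0.884 above.

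Power falls because the estimate shrinks while its reported standard error does not. With arm out and baseline in, under purely random missingness, the mean was 0.903, the reported standard error 0.427 and the actual spread 0.312. Then (0.903 − 2 × 0.427)/0.312 = 0.16, and Φ(0.16) = 0.56, in line with the simulated 57%.

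**Simulation, patient outcome.** 64 clinics × 7 patients, true effect 0.5 SD, ICC 0.03, correlation 0.5, 1,500 trials. The 25% missing fraction is an assumption, because the protocol gives that figure for GPs only.
- Arm out: 0.376, against 0.75 × 0.5 = 0.375.
- Arm in, clinic out: 0.501, with reported standard error 0.0998 against an actual spread of 0.1009.
- Arm in, baseline out: 0.501.

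By the same formula the patient estimate with arm out would be 0.45 at 10% missing and 0.325 at 35%.

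**The case against.** **The text does not exclude arm.** It names variables that will be used and does not say that no others will be. The candidate set is open-ended, and a competent analyst would probably include arm anyway. This stands: the omission is permitted, not ordered. But the sentence gives one criterion and nothing else, and an analysis plan that followed it literally would inherit the fault.

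**Listing imputation variables is work for the analysis plan.** A bare missing list would indeed be no finding in an article. Here the article goes further and states how variables are chosen. That is a rule fixed badly, and it can be corrected where it stands.

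**The simulated missingness would not trigger imputation on a literal reading.** Missingness unrelated to the outcome, or explained by a recorded covariate, is compatible with missing at random, whereas the plan imputes when that is judged not to hold. This limits the figures: they show what the variable rule does once imputation is run with similar dropout in the arms, not how often that will happen. Still, a search among recorded factors can only reveal dependence on those factors, so finding some is likely to be what sets off imputation in practice.

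**The imputed result may not replace the main one.** The paragraph sits under Secondary analysis and does not say that imputation supersedes the multilevel model. This also stands. If imputation is not triggered, that model on the available data is unaffected.

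A reader might go further and infer that leaving out baseline or clinic also pulls the effect towards zero. The calculations do not support this. Omitting baseline alone left the estimate unbiased and cost at most a few points of power. Omitting clinic alone left it unbiased at ICC 0.03. Clinic matters mainly for the between-clinic variance in the patient data, and hardly at all for the primary outcome with one GP per clinic.

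**Conclusion.** The point holds in a conditional form. The article selects imputation variables by whether they predict missingness and does not require the analysis-model terms. If imputation is triggered, dropout is similar between arms and the rule is followed literally, arm can be left out. The arm effect then shrinks by about the missing fraction: from 1.2 to about 0.90 at the planned 25% GP dropout, with power falling from about 78–80% to about 53–59%. These figures assume one GP per clinic, equal allocation, a missing share equal to the dropout rate, and a baseline-adjusted linear analysis.

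The patient outcomes face the same risk, but its size depends on a missing fraction that the protocol does not give. The documents do not support saying that the primary result will be diluted. They support saying that the stated rule does not prevent it.

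**What to change.** Replace the imputation clause with wording such as: *Any multiple imputation will include all variables of the analysis model (arm, time-point, the stratification factors and, for patient data, clinic as a level) and the other baseline and follow-up scores of that outcome; predictors of missingness will be added as auxiliary variables.* Imputing separately by arm is an acceptable alternative for protecting the arm contrast.

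This is one sentence in the protocol or the analysis plan and needs no new data. The cost is slightly more programming, mainly for multilevel imputation of the patient outcomes.

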### Data monitoring

A data monitoring committee will meet quarterly to review study data during the period of recruitment and intervention, and interim analysis will be supplied to the Executive Team at scheduled occasions and on request and in confidence.

### Harms

We do not anticipate any harms to GP or patient participants as a result of participating in this study.

## Discussion

The challenges described by some GPs when managing work-related mental health conditions reflect gaps in knowledge as well as the absence of pragmatic effective strategies to implement Guideline recommendations and a likely lack of confidence in implementing these strategies [4, 11]. The IMPRovE intervention will address these challenges using a complex intervention that comprises academic detailing, a community of practice, and the provision of resources to improve Guideline-concordance amongst participating GPs.

Firstly, tailored academic detailing will be provided to each GP cluster in the intervention. This session will be led by a GP opinion leader, who will introduce the Guideline, identify evidence-based practice gaps in current clinical practice, and provide GP participants with practical and tailored strategies during the academic detailing session. This phase of the intervention will raise awareness of the issue amongst participants, highlight areas of behaviour change in their own practice, and create an initial sense of enthusiasm regarding implementing the Guideline recommendations. Secondly, the digital community of practice will provide GPs with opportunities to increase their learning; receive advice about other clinical dilemmas that were not addressed in the initial academic detailing session, or test and adjust their own practices; and assist their colleagues to develop implementation strategies for a range of issues related to mental health conditions that have arisen as a result of work. Engagement with the GP opinion leader will continue on the community of practice platform, thus re-enforcing the credibility of discussions and learnings on the community of practice. Finally, during the academic detailing session, GP participants will receive a suite of resources that can assist them to implement the Guideline, along with advice about how to use these resources (e.g. to monitor patient improvement), and a more comprehensive resource library will be offered via the community of practice.

The IMPRovE intervention has been constructed in response to the self-reported barriers that sometimes prevent GPs from providing optimal care for people with work-related mental health conditions [11], as well as theoretical principles of normalisation process theory [15]. As the IMPRovE intervention involves both peers and opinion leaders, they offer participating GPs the peer-to-peer social influences that are well regarded by clinicians when making choices about their clinical practice [17]. The flexible nature of the academic detailing session enables the GP opinion leader to adapt a session so that it meets the needs of the GP participants [20]. Similarly, the flexible nature of a community of practice enables clinicians to choose what topics they engage with and how [45]. Providing GPs with credible and relevant resources will equip GPs with practical tools for use in their clinical practice [28]. Together, the intervention components are likely to improve guideline concordance because they are based on social interactions, tailored to the needs of participating GPs, accompanied by credible and evidence-based advice from opinion leaders, and reinforced over a period of time [15, 16, 18].

The IMPRovE intervention has also been designed with acceptability and sustainability in mind. The intervention and its components were created in collaboration with a reference group of GPs and researchers, as well as an intervention advisory group that included GPs, mental health consumers, and representatives of workers’ compensation schemes. A steering group comprising members from three key clinical organisations (representing Australian GPs, psychologists and psychiatrists, respectively) as well as representatives of compensation agencies and a key non-government mental health organisation, *Beyond Blue*, also provided advice and guidance about the health system and policy context. Co-design with GPs who are the end-users of the intervention, and with policy makers who influence the compensation landscape and have the capacity to sustain the intervention into the future, should yield a more effective and sustainable intervention.

Finally, the IMPRovE trial has been designed using a practical approach to maximise feasibility. For instance, whilst guideline concordance would ideally be measured in routine clinical practice, GPs in our trial are likely to see a relatively small number of patients with work-related mental health conditions each year. Consequently, we have chosen to use virtual simulated patient scenarios as a practical yet rigorous approach to measuring our primary outcome of guideline concordance. We have also chosen this method of assessment due to the nature of the Guideline recommendations, which provide no specific outcomes that can be audited in a case note analysis. For instance, outcomes such as “consideration of social factors, or symptoms that may indicate comorbidities” may not be recorded in case notes, even if a GP does consider these factors in their clinical decision-making process. All secondary outcome measures are based on widely used pre-existing surveys or scales using established methodologies.

## Conclusions

Researchers, governments, and guideline developers invest significant time and funds to facilitate guideline implementation in primary care. The IMPRovE study will assess the effectiveness of a complex intervention on guideline implementation in the context of work-related mental health conditions. If this intervention proves to be effective and cost-effective, the IMPRovE study will chart a clear path to evidence-informed care for people with work-related mental health conditions.

## Data Availability

Trial data can be obtained upon request from the corresponding author.

## Abbreviations

DMC: Data Monitoring Committee
GP: General practitioner
IMPRovE: Implementing work-related Mental health conditions in general PRacticE
ICC: Intraclass correlation coefficient
